# Distinct exercise modalities on GUT microbiome in sarcopenic older adults: study protocol of a pilot randomized controlled trial

**DOI:** 10.3389/fmed.2025.1504786

**Published:** 2025-03-05

**Keywords:** muscle quantity, muscle quality, aerobic exercise, resistance exercise, concurrent exercise, gut microbiota, sarcopenia, older adults

## Abstract

**Background:**

Sarcopenia is a progressive and age-related skeletal muscle disease related to adverse health outcomes and to an increased economic burden. Recent evidence pinpoints the human gut microbiota (GM) as a contributing factor in the development of sarcopenia via the gut-muscle axis. To date, no study specifically analyzed the optimal type of exercise modality in older adults with sarcopenia considering the impact of GM composition in skeletal muscle mass and function. Therefore, the DEMGUTS study intents to explore the impact of three different exercise regimens on GM composition and gut-derived metabolites in older adults with sarcopenia.

**Methods:**

This pilot single center three-arm parallel open-label randomized control trial (RCT) will randomly assign eligible participants to: (i) moderate aerobic exercise (AER); (ii) resistance exercise (RES); or (iii) concurrent exercise training (RES + AER). Participants will engage in a supervised center-based exercise intervention (12-weeks, 3 d/week, 60 min/d), and will be assessed at (i) baseline, (ii) end of intervention (14 weeks), and (iii) at close-out (26-weeks). The primary outcome will be the change in the relative abundance of *Faecalibacterium prausnitzii* and other short-chain fatty acid producing bacteria after the intervention (14-weeks). A set of complementary outcomes will also be assessed to broadly characterize the impact of each exercise intervention on body composition, skeletal muscle function, functional performance and general GM composition.

**Conclusion:**

Unraveling the impact of these exercise regimens on GM is crucial to help clarify the optimal exercise modality to manage sarcopenia disease, contributing to clinical guidance and enhancing exercise prescription in older adults with sarcopenia.

**Clinical trial registration:**

https://clinicaltrials.gov/, identifier NCT06545123.

## Introduction

1

Sarcopenia is a progressive age-related skeletal muscle disorder (1–5) associated with adverse health outcomes, predictor of chronic disease progression, physical dysfunction, poor quality of life and premature death (4, 6–8). The prevalence of sarcopenia ranges from 10% in healthy adults over 60 years of age to 33% in people in long-term care (9). The mechanisms that contribute to the onset of sarcopenia are multifactorial and not fully understood (10). The combination of neurological factors – loss of motor neurons and motor units –, endocrine and lifestyle changes related to physical activity (PA) levels and nutrition also appear to contribute to the onset of sarcopenia (11). Hormonal and cytokine imbalances, age-related chronic inflammation (i.e., inflammaging) and metabolic disorders—namely insulin resistance have also been described as pathophysiological mechanisms involved in sarcopenia (11). The interplay of all these mechanisms reduces the expression of skeletal muscle anabolic factors and activate skeletal muscle catabolism pathways (11).

Recent evidence highlights the human gut microbiota (GM) as a new contributing mechanism to the development of sarcopenia (10). The decrease in gut biodiversity and function and the disruption in the composition of bacteria strains with health-promoting activity, such as *Bifidobacteria, Lactobacilli*, *Faecalibacterium prausnitzii, Eubacterium* spp., *Roseburia* spp., and *Ruminococcus* spp. are associated with the aging process and also to sarcopenia (12–15). Moreover, gut dysbiosis is associated to reduced muscle size, impaired muscle function and adverse clinical outcomes; the mechanisms underlying this relationship are still unclear.

It is known that gut microbiome composition may vary due to multiple endogenous and environmental factors such as diet, physical activity and medication or supplementation use and may confound the causal relationship between gut microbiome and sarcopenia (16). Still, gut dysbiosis contributes to gut barrier dysfunction, increasing its permeability, favoring the translocation of microbial byproducts such as lipopolysaccharides into the blood stream (1, 11, 17). This process aggravates age-related low-grade chronic inflammation and increases insulin resistance, mechanisms that are involved in the onset of sarcopenia (1, 11).

The effect of exercise on the GM composition has been analyzed qualitatively and quantitatively and is mostly associated with positive results in the aging process (18, 19). For instance, the increase in exercise levels is associated with a decrease in the relative abundance of potentially pathogenic taxa, higher microbiota biodiversity and butyrate production taxa (18), whereas a sedentary behavior is associated with gut dysbiosis, growth of pathogenic opportunists bacteria strains and alterations on GM functionality (20). Higher proportions of *Akkermansia, Faecalibacterium prausznitzii, Roseburia hominis*, and *Bifidobacterium spp*- known for its anti-inflammatory health benefits were observed in active women and athletes (14). Further, exercise training decreased the abundance of bacteria associated with intestinal dysbiosis, suggesting that exercise stimulates healthy gut microbes, in addition to improving muscle in physically active individuals (1). Despite these positive effects of exercise training on GM in young adults, the findings in older adults are less clear and conflicting, changes appear to be transient and reversible and to date, the effects of exercise training on GM in patients with sarcopenia remains unclear (21, 22).

The available evidence suggests that different types of exercise modalities may elicit distinct alterations in GM composition. Aerobic and resistance exercise activate different molecular pathways. Aerobic training (AER) improves the permeability of intestinal barrier, promotes bacterial taxa related to aerobic capacity and SCFA production whereas resistance exercise (RES) may enhance the composition of bacterial strains associated to muscle strength, upregulate anti-inflammatory cytokines and reduce endotoxemia (18, 23, 24). Given that these two exercise training regimens activate different bioenergetic signaling pathways [i.e., AER- activates the transient activated protein kinase (AMPK) pathway whereas RES activates the longer-lasting mechanistic target of rapamycin (mTOR)], we can hypothesize that each regimen promotes distinct alterations on GM, whereas the combination of both forms of exercise (resistance + aerobic) may lead to a complementary or added effect. There is limited evidence on the effects of concurrent training on sarcopenia outcomes, but the scarce evidence highlights the positive effects of combining both forms of exercise training on body composition, skeletal muscle regeneration and cardiorespiratory fitness (25). However, to date, no studies specifically analyzed the impact of different exercise training regimens (i.e., resistance, aerobic and concurrent exercise training) on GM composition and investigated its effects on skeletal muscle mass and function in older adults with sarcopenia. Thus, we designed a pilot three-arm randomized controlled trial (RCT) to unravel the effect of these exercise regimens on GM to help clarify the optimal exercise mode to manage sarcopenia and, we hypothesize that the combined exercise training mode may elicit more benefits on GM composition and function, on gut health and physical performance than each exercise training regimen alone.

## Methods

2

### Study design

2.1

The DEMGUTS project is a three-arm pilot RCT designed to evaluate the impact of different exercise training regimens on GM composition and on skeletal muscle mass and functionality in older adults with sarcopenia (age ≥ 60 years). This project was designed through a collaborative effort of a multidisciplinary team of experts in microbiome, exercise training and metabolomics. This project fulfilled all ethical procedures including the approval of the FADEUP ethics Committee (approval #CEFADE 4) and was registered on a public database (clinical trials: NCT06545123). This study followed strict guidelines to ensure participant safety and protection as recommended by the Helsinki Declaration (26).

### Participant recruitment

2.2

Eligible volunteers will be recruited through an established collaboration with the community exercise program “*Mais e Melhores Anos*” at Famalicão. The inclusion criteria in our trial are based on the diagnosis criteria defined by the EWGSOP2 (27, 28) and thus, our goal is to enroll participants that have low skeletal muscle strength and quality. The assessment of eligibility will be made in two phases. In the first phase, prior to the screening visit, two members of the research team will analyze physical performance tests records collected in two different time points (October 2023 and June 2024), to identify eligible volunteers. Men and women who present handgrip test values below the sarcopenia cut-off point (men <27 kg and women <16 kg) will then be invited to an in-person screening visit to continue the eligibility assessment process. In this in-person assessment visit and prior to enrolment, − the second phase, each volunteer will receive a detailed explanation of all study phases and procedures, the benefits and risks along with all participant duties. Those that agreed to participate will provide their written informed consent as mandated by the Helsinki Declaration and its later amendments to protect human research (26). Afterwards, volunteers will be evaluated through additional complementary clinical and functional tests, including the assessment of body composition through dual-energy x ray absorptiometry, the Short Physical Performance Battery, the 4 meters gait speed, the 400 meters long distance corridor test, and through a handgrip dynamometry test—objective indicators of sarcopenia (27, 28), to confirm their eligibility. Those who met all the inclusion/exclusion criteria will be randomly assigned to one of three different exercise training interventions: (i) aerobic exercise (AER) training; (ii) resistance exercise (RES); or (iii) concurrent training (RES + AER).

#### Inclusion/exclusion criteria

2.2.1

Participants will be included if: (*a*) aged ≥60 years; (*b*) present objective indicators of sarcopenia recommended by the EWGSOP2 [handgrip strength: men <27 kg and women <16 kg + appendicular skeletal muscle index/ height^2^: men <7.0 kg/m^2^ and women <5.5 kg/m^2^; severity will be assessed by the 4-m gait speed ≤0.8 m/s; SPPB ≤8-point score; Chair stand test >15 s; Time-up-go ≥20 s]; (*c*) level of PA ≤150 min/week of moderate PA assessed using the International Physical Activity Questionnaire (IPAQ)- Portuguese version (29); (*d*) Willingness to participate in all study procedures regardless of possible group allocation. In contrast, participants will be excluded if: (a) fail to provide consent; (b) present uncontrolled hypertension: (c) Systolic Blood Pressure (SBP) > 180 mmHg or Diastolic Blood Pressure (DBP) > 110 mmHg; (d) history of coronary artery stenosis (>50%); (e) heart failure: ejection fraction <50%; (f) history of syncope at exertion; (g) history of hypertrophic cardiomyopathy; arrhythmogenic cardiomyopathy, dilated cardiomyopathy or evidence in the previous 6 months of myocarditis or pericarditis; (h) severe valvular heart disease; (i) chronic kidney disease stage ≥4.8; (j) chronic obstructive pulmonary disease stage ≥3.9; (k) musculoskeletal or neurodegenerative conditions that hinders exercise engagement; (l) current participation in another structured exercise training program; (m) inability to commit to study procedures or the exercise intervention throughout the study period; (n) other condition or concern precluding safe participation.

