#### Sample size

2.2.2

The sample size was calculated based on a previous study (3) were authors saw a large effect after the intervention (Cohen d’s effect size = 1.15). Given that to date, there are no consensus in the optimal method to analyze microbiome health status, we selected the change on the relative abundance of *Faecalibacterium prausnitzii* and other SCFA (Short-Chain Fatty Acid) producing bacteria after the intervention (12-weeks) as our primary outcome. Nonetheless, this pilot study was powered to detect a more conservative effect size- of 0.9 on *Faecalibacterium prausnitzii* relative abundance after the intervention between experimental groups. Assuming an 80% power, a two-sided significance level of 0.05, we would need a total of 21 participants/group (calculated on GPower version 3.2). With an allocation ratio of 1:1:1 and an attrition rate of 10%, the final sample is of *N* = 69 (*n* = 23/group) participants.

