### Assessments

2.5

Participants will be evaluated in three different moments: (i) baseline; (ii) end of the intervention (12 weeks); (iii) close-out (24 weeks). The study has a total duration of 26 weeks. In each study visit, participants will perform the same physical and functional assessments, body composition analysis, and provide a fasting blood and feces sample. Other confounding variables will also be recorded, including nutritional intake (through a 3-day diary), daily PA levels (through a PA tracker), medication intake. Medication and supplementation along with other associated comorbidities will be assessed using a medical questionnaire and medication history questionnaire. Considering the study design, the following outcomes will also be evaluated: (a) retention and attrition rates; (b) adherence to exercise intervention; (c) safety; (d) intervention effect on dependent outcomes (Table 4).

**Table 4 tab4:** Overview of the assessment visits and data collection at each visit.

Study phase	Pre-randomization		Intervention		Follow-up
Visit description	Screening	Baseline	Start	End	CO
Visit number	1	2	3	4	5
Week number	−2	0	2	14	26
Informed consent, review inclusion/exclusion criteria	x				
Demographic information, medical history, medication use	x				
IPAQ questionnaire	x				
Office blood pressure	x	x	x	x	x
Anthropometry measurements	x	x		x	x
Randomization	x				
Body composition (DEXA)		x		x	x
Blood and fecal samples for study assays		x		x	x
Nutritional Intake		x		x	x
Skeletal muscle strength		x		x	x
Physical performance testing		x		x	x
Daily physical activity		x	x	x	x
Assess adverse events			x	x	x
Exercise intervention			x	x	

CO, close-out.

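### No entry criterion in section 2.2.1 deals with recent antibiotic use or any other gut confounder, although the trial is powered on a gut bacterium; deferring the baseline stool would be a cheap improvement

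*Protocol article*

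**What the plan says.** Section 2.2.1 gives four inclusion criteria and fourteen lettered exclusions. The exclusions begin "In contrast, participants will be excluded if: (a) fail to provide consent; (b) present uncontrolled hypertension" and go on through cardiac, renal, pulmonary and musculoskeletal or neurodegenerative conditions, other exercise programmes ("l) current participation in another structured exercise training program") and inability to commit. The last item reads "n) other condition or concern precluding safe participation", so it is tied to safety. Nothing in either list mentions antibiotics, probiotics, bowel disease or bowel surgery.

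The Introduction says that microbiome composition may vary with "diet, physical activity and medication or supplementation use and may confound the causal relationship between gut microbiome and sarcopenia". Section 2.5 responds by recording: "Other confounding variables will also be recorded, including nutritional intake", with physical activity, medication, supplementation and comorbidities also collected. Table 4 marks medication use at the screening visit only. Section 2.3 names daily physical activity as a covariate for the primary outcome; the article names no medication covariate.

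On size, section 2.2.2 cites a study where "authors saw a large effect after the intervention (Cohen d’s effect size = 1.15" was reported, then states that "this pilot study was powered to detect a more conservative effect size- of 0.9". It continues "Assuming an 80% power, a two-sided significance level of 0.05" and arrives at 21 per group, raised to 23 for attrition.

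**The concern.** The primary outcome is a change from the baseline stool to the end-of-intervention stool. If the baseline sample is taken soon after a course of antibiotics, part of the later change may be recovery from the drug and not a response to exercise. The protocol's own reasoning points to this. It names diet, physical activity and medication or supplementation as influences. Physical activity is restricted at entry and used as a covariate. Diet is recorded before each stool, and the first diary is handed back to help standardise intake (section 2.5.4). Medication is only recorded.

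At stake are the precision of a small three-arm comparison and, because section 2.4.1 says the data will refine the sample size of a full-scale trial, the SD carried forward to that trial.

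**Working it through.** **1. Entry rules.** Going through (a) to (n): none is a gut criterion. Item (l), with inclusion (c), does restrict one influence that the Introduction names, physical activity. No item restricts medication or supplementation. Item (n) would not stop someone who is safe to exercise but has recently taken antibiotics.

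**2. The plan's own figure.** Two-sample t-test, two-sided α = 0.05, d = 0.9, n = 21 per arm: degrees of freedom 2 × 21 − 2 = 40, noncentrality 0.9 × √(21/2) = 2.92, power 81.2%. With 20 per arm it is 79.2%. So 21 reproduces, with little slack.

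**3. Illustration of the extra variance.** The documents give no raw SD, no exposure rate and no size of shift; all three are assumed here. Let a share p of each arm be exposed and their change score shift by k SD. The SD is then multiplied by f = √(1 + p(1 − p)k²). Power was simulated with 100,000 replicates, n = 21 per arm and the same raw difference (0.9 SD of the unexposed change):

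| p | k | f | Unadjusted power |
|---|---|---|---|
| any | 0 | 1.00 | 81% |
| 5% | 1 | 1.02 | 79.5% |
| 5% | 2 | 1.09 | 74.5% |
| 5% | 3 | 1.19 | 67.1% |
| 10% | 1 | 1.04 | 77.7% |
| 10% | 2 | 1.17 | 68.5% |
| 10% | 3 | 1.35 | 56.8% |

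So the range is about 57–80%, and 81% if nobody is exposed or exposure does nothing.

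**4. Can recorded exposure repair it?** Add one exposed/unexposed covariate, estimated across all three arms (63 people; 63 × 0.05 ≈ 3 to 63 × 0.10 ≈ 6 exposed). If every exposed person shifts by the same k, power returns to 81–82% in all six scenarios (8,000 replicates each). If the shift varies between people with an SD of half its mean, power with the covariate is about 74–81%.

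**5. Chance imbalance.** Two exposed people in one arm and none in another move the contrast by 2k/21 = 0.10, 0.19 or 0.29 SD for k = 1, 2, 3. One standard error of the contrast is √(2/21) = 0.31 SD. A difference of at least two between a given pair of arms arises in about 26% of trials at 5% exposure and 43% at 10%. This is the same randomness that lowers power in step 3, so the two must not be added.

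**6. The discount in the planning effect.** At a fixed raw difference, going from 1.15 to 0.9 is equivalent to an SD 1.15/0.9 = 1.28 times larger. Five of the six values of f above lie below 1.28. Starting from d = 1.15, power after dividing by f is 94%, 92% and 86% at 5% exposed, and 94%, 88% and 77% at 10%.

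**The case against.** The strongest reply is that broad entry with recording and adjustment is a legitimate choice for a pilot that recruits from one community programme. The article collects medication, supplementation and comorbidities as confounders and plans mixed models, and the full covariate list may sit in an analysis plan that is not shown. Step 4 bears this out: a reader might infer that too few people per arm would be exposed for recording to help, but a covariate pooled over the arms recovers most or all of the loss. That part of the reply stands.

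A reader might also infer that recovery after antibiotics would masquerade as an exercise effect. The hypotheses in section 2.6 are between randomised groups, so recovery is equal across arms in expectation. It would distort a within-arm change, but it does not systematically bias the comparison.

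Nor do the documents show that the 80% power claim is wrong. The planning effect was reduced from the published one. The article does not say what the reduction is for, and the cited study's eligibility is not shown, so its SD may already include such people.

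What the reply does not remove is the entry rule. Eligibility belongs in the protocol, the list is printed in lettered detail, and it leaves open one of the influences that the Introduction names. Adjustment also needs exposure to be known at each stool, whereas Table 4 marks medication use at screening only.

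**Conclusion.** The point holds as a cheap design improvement. No eligibility criterion covers a gut confounder, the catch-all is confined to safety, and recently exposed people can enter a change-from-baseline comparison of a gut bacterium. The consequence is non-exercise variance and possible chance imbalance, smaller than one standard error for two exposed against none.

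Its size cannot be derived from the documents. The 57–80% range in step 3 is illustrative: it rests on an assumed 5–10% exposure, an assumed 1–3 SD shift in one direction, and no adjustment. The case for deferral concerns antibiotics. No calculation here supports excluding bowel disease; a stable condition need not shift a within-person change.

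**What to change.** - In section 2.2.1, defer baseline stool collection and randomisation for anyone with systemic antibiotics within a look-back that the investigators fix in advance. People are delayed, not rejected. The medication history taken at screening (week −2 in Table 4) comes before the baseline stool (week 0), so the information is already to hand.
- Record antibiotic exposure at every stool visit, and align Table 4 with the section 2.5 text on medication.
- Keep participants exposed after baseline in the intention-to-treat analysis, and prespecify one further analysis that adjusts for exposure or omits them.
- Optionally, consider whether active bowel disease or previous bowel resection should be an exclusion. This is a trade-off against recruitment and breadth of population, and it is for the investigators to judge.

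The cost is one amendment to the eligibility text, a few delayed enrolments and one extra model.

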#### Sample size

2.2.2

The sample size was calculated based on a previous study (3) were authors saw a large effect after the intervention (Cohen d’s effect size = 1.15). Given that to date, there are no consensus in the optimal method to analyze microbiome health status, we selected the change on the relative abundance of *Faecalibacterium prausnitzii* and other SCFA (Short-Chain Fatty Acid) producing bacteria after the intervention (12-weeks) as our primary outcome. Nonetheless, this pilot study was powered to detect a more conservative effect size- of 0.9 on *Faecalibacterium prausnitzii* relative abundance after the intervention between experimental groups. Assuming an 80% power, a two-sided significance level of 0.05, we would need a total of 21 participants/group (calculated on GPower version 3.2). With an allocation ratio of 1:1:1 and an attrition rate of 10%, the final sample is of *N* = 69 (*n* = 23/group) participants.

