### Statistical analysis

2.6

Descriptive and exploratory analyses will be performed, and normality will be assessed using the Kolmogorov–Smirnov or Shapiro–Wilk tests, and if necessary, the data will be transformed for normalization. The differences between the baseline groups will be explored using one-way analysis of variance (ANOVA) or Kruskal-Wallis tests for continuous data and chi-square tests for categorical data.

The intention-to-treat principle will be used for the primary outcome analysis. The main analyses will employ random coefficient linear mixed models for normally distributed endpoints or generalized mixed models for non-normally distributed endpoints. Post-hoc analysis with Bonferroni correction will assess differences between treatment factors. Cohen’s d will be used to indicate the effect size, and significance will be set at *p* < 0.05.

Fecal samples will undergo taxonomic analysis, grouped into amplicon sequence variants (ASVs), and summarized at different taxonomic levels. These data will be imported in R for use with the Phyloseq package. Several indices of alpha and beta diversity will be evaluated (i.e., Simpson Index, Shannon-Wiener Index, Bray–Curtis dissimilarity, Unweighted and weighted Uni-Frac for beta-diversity). Principal Coordinate Analysis (PCoA) will be performed to visualize the dissimilarity matrix between all samples and a PERMANOVA on exercise groups will be performed. Analysis of Compositions of Microbiomes (ANCOM) with bias correction will be used to test for differential abundance of individual ASVs at several levels to compare the three exercise groups. We will use the Benjamin– Hochberg corrected significance level of 0.05 to minimize false discovery rate (FDR). For the metabolomics analysis, samples will be normalized by the total ion current and means centered using Pareto scaling. Univariate analysis of variance will be performed on data from both ion modes to identify variations in peak areas between groups at baseline and after the 12-weeks intervention. Partial least squares discriminant analysis (PLS-DA) will be used to detect the most critical discriminant metabolites in each comparison across groups consistent with published guidelines for metabolomics trials (36). Microsoft packages (e.g., Excell), SPSS (version 27) and R (version 4.2.) software will be used to manage and analyze the different data.

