The study primary null hypothesis are: (a) there are no differences in *Faecalibacterium prausnitzii* and other SCFA-producing bacteria after the intervention between groups; (b) there are no differences in *Faecalibacterium prausnitzii* and the other SCFA-producing bacteria after the intervention between the RES + AER group versus the AER group; (c) there are no differences in *Faecalibacterium prausnitzii* and other SCFA-producing bacteria after the intervention between the RES + AER group vs. the RES group. We hypothesize that combining AT and RT will have a greater impact on the GM composition, specifically in increasing the relative abundance of *Faecalibacterium prausnitzii* and other SCFA producing bacterial strains, an increase in skeletal muscle mass and strength, as well as enhanced physical performance measures in the concurrent exercise training group.

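### The stated 80% power fits one unadjusted two-group test; the Bonferroni-corrected primary contrasts have about 66–73% power at the planned effect

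*Protocol article*

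**What the plan says.** In the protocol article, the sample size section (2.2.2) states "this pilot study was powered to detect a more conservative effect size- of 0.9 on" *Faecalibacterium prausnitzii* relative abundance between the experimental groups. It continues: "Assuming an 80% power, a two-sided significance level of 0.05, we would need a total of 21 participants/group". The software is named ("calculated on GPower version 3.2"), but the statistical test is not, and no multiplicity adjustment is mentioned. The section then sets the final sample at 69, or 23 per group.

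The statistical analysis section (2.6) specifies mixed models as the main analysis and adds: "Post-hoc analysis with Bonferroni correction will assess differences between treatment factors". It does not say how many comparisons the correction covers.

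The same section closes with the hypotheses: "The study primary null hypothesis are: (a) there are no differences in" the bacterial outcome between groups, which is the global null. Null (b) is RES+AER against AER, and null (c) is RES+AER against RES. The directional hypothesis, in the introduction and again in 2.6, is that concurrent training does better than either modality alone.

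**The concern.** The power statement is tied to a two-sided 0.05. Contrasts (b) and (c) are primary, and if they are tested with the planned Bonferroni correction, each is judged at 0.025 or about 0.0167. A power figure computed at 0.05 does not describe those tests.

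Two things are at stake. First, the trial's leading claim needs (b) and (c) to be rejected together, which is harder than rejecting either one. If that fails, a reader who has the 80% figure in hand may take the result as stronger evidence against a 0.9 SD effect than it is. Second, the primary aim section (2.4.1) says these data will help refine the sample size of a full-scale trial, so a calculation that omits the correction could be carried forward.

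**Working it through.** **Inputs.** From 2.2.2: d = 0.9 (read as Cohen's d, because the earlier study's 1.15 is given as Cohen's d), two-sided α = 0.05, 80% power, n = 21 per group. From 2.6: two named pairwise contrasts, and Bonferroni with no stated divisor. The divisor is therefore taken as 2 (only the named contrasts) or 3 (all pairs of three arms). SD is set to 1. The calculation covers *F. prausnitzii* alone.

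**Reproducing 21 per group.** Two-sample t-test: noncentrality δ = d·√(n/2) = 0.9·√10.5 = 2.916, df = 2·21 − 2 = 40, critical t = 2.021.
- n = 21: power 81.2%. n = 20: power 79.2%. So 21 is the smallest n that reaches 80%.
- Alternatives tried: normal approximation, 20; one-sided t-test, 16; three-group F-test, 19 (one arm differs by 0.9) or 25 (third arm midway).

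Only the unadjusted two-sided t-test gives 21. The test is inferred, not stated.

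**Power per contrast after Bonferroni** (δ = 2.916, n = 21):

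| Divisor | α | Critical t (40 df) | Power, two-sample | Power, three-arm pooled variance (60 df) |
|---|---|---|---|---|
| 1 | 0.05 | 2.021 | 81.2% | 81.8% |
| 2 | 0.025 | 2.329 | 72.0% | 73.0% |
| 3 | 0.0167 | 2.499 | 66.2% | 67.5% |

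With no dropout at all (23 per group), the figures are 76.5–77.4% (divisor 2) and 71.2–72.3% (divisor 3), still under 80%.

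**Detectable effect.** Solving the two-sample formula for d at 80% power and n = 21 gives 0.886 (α = 0.05), 0.983 (0.025) and 1.036 (0.0167).

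**Group size for 80% per contrast at d = 0.9.** 25 evaluable per group (divisor 2) or 28 (divisor 3), against 21.

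**Both (b) and (c) rejected.** Simulation with pooled variance and means AER = 0, RES = 0, RES+AER = 0.9: 60% (divisor 2), 53% (divisor 3).

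**Global hypothesis (a).** F-test with 2 and 60 df, critical F = 3.150, λ = n·Σ(μᵢ − μ̄)².
- Only RES+AER differs (0, 0, 0.9): λ = 21 × (0.09 + 0.09 + 0.36) = 11.34; power 84.5%.
- One arm midway (0, 0.45, 0.9): λ = 21 × (0.2025 + 0 + 0.2025) = 8.505; power 72.3%.

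**Gatekeeping alternative.** Test (a) at 0.05 and, only if it is rejected, test the pairwise contrasts at 0.05 each. Simulated at n = 21:
- Only RES+AER differs: 78% per contrast, 71% for both.
- One arm midway: 71% for the larger contrast, 29% for the smaller, 28% for both.
- All arms equal: family-wise error 5.0%, against about 12% for three uncorrected pairwise tests.

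**The case against.** **The plan does not Bonferroni-correct three primary hypotheses.** A reader might infer this from the three listed nulls and quote only the divisor-three figure. The text does not support it. The correction is stated for post-hoc comparisons, nothing says the global null is corrected, and no divisor is given. This stands, and it is why the result is a range of about 66–73%.

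**The 80% is not wrong for everything in the plan.** Hypothesis (a) has 84.5% power if only RES+AER differs. This also stands, although it falls to 72% if one arm lies midway. The mismatch concerns (b) and (c).

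**The analysis is a mixed model, not a t-test.** If 0.9 is in raw SD units, baseline adjustment turns it into 0.9/√(1 − ρ²). Under assumed correlations of 0.3, 0.4 and 0.5 the effect becomes 0.943, 0.982 and 1.039, and power at α = 0.0167 is 71%, 75% and 80%. If 0.9 already refers to an adjusted or change-score SD, this gain does not apply in that form. The article gives no correlation and does not invoke one in its sample size, so the percentages depend on this. The possibility neither establishes nor rules out 80%.

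**It is a pilot.** True, and this limits the consequence. But the section says in terms that the study was powered, so the claim should match the analysis.

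**Attrition.** A reader might add that 69 does not cover the 10% loss, since 69 × 0.9 = 62.1 against 63. This is rounding: 21 × 1.1 = 23.1, the gap is under one participant, and unadjusted power at 20.7 per group is still 80.6%. It is not part of the point.

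**Conclusion.** The point holds for the two pairwise primary contrasts. Under either plausible divisor, the stated 80% falls to about 72–73% or 66–68% per contrast. The joint claim that concurrent training beats both other modalities has about 60% or 53%.

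This rests on reading 0.9 as Cohen's d, on 21 evaluable per group, on no gain from baseline adjustment and, for the joint figures, on equal AER and RES means. With one of those arms midway, the joint power is lower.

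It does not follow that the trial is too small to be worth running, or that the global hypothesis is underpowered in every configuration. This is a statement that should be corrected, not a defect that invalidates the design.

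**What to change.** Keep N = 69. In 2.2.2, name the test behind the 21 per group, state which contrasts form the primary family and hence the Bonferroni divisor, and replace the 80% figure with one that belongs to that family:
- divisor 2: about 72–73% power at d = 0.9, or a detectable d of about 0.98;
- divisor 3: about 66–68% power at d = 0.9, or a detectable d of about 1.04.

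If baseline adjustment is relied on for more power, state the assumed correlation and the SD to which 0.9 refers. In 2.6, give the same divisor.

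As an option, not a requirement, the order in which the hypotheses are listed could be used as a gate: (a) at 0.05, then the pairwise contrasts at 0.05 only if (a) is rejected. With exactly three arms this controls family-wise error at 5%. The gain depends on the configuration, as shown above, and even the favourable case stays just below 80% per contrast, so the power would have to be restated here too.

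The cost is wording in two sections and a less favourable power figure. No participants are added.
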